### EEG Features Across Changes in Sedation Status

Changes in the aforementioned EEG features (i.e., spectrograms, topographic maps, wPLI, dPLI, graph theoretical network properties and hubs) between the three phases (i.e., baseline continuous sedation; interruption of sedation; and return of continuous sedation) will be used to assess the brain’s ability to adaptively reconfigure its networks in response to changes in level of anesthesia; the degree of adaptive reconfiguration will be used as predictors of outcome.

### Auditory Narrative – Inter-Subject Correlations and Correlated Components Analysis

We will examine the inter-subject synchronization between each patient and healthy participants (database already acquired). The data will be interrogated using a ‘bottom up’ data-driven correlated components analysis (CorrCA; Dmochowski et al., 2012; Cohen and Parra, 2016; Ki et al., 2016), which is ideal for continuous naturalistic stimuli like movie narratives (Laforge et al., in press). The CorrCA is one method to calculate inter-subject neural synchronization (inter-subject correlations)—a common index of shared neural processing during movie tasks—across a group (Dmochowski et al., 2012; Naci et al., 2014, 2017; Ki et al., 2016). The basic CorrCA procedure is as follows: the CorrCA is a non-parametric data reduction technique that extracts a pattern of electrode activity that is maximally correlated across participants during the movie task. This pattern represents the common neural response to its auditory and linguistic features and importantly, its plot (Dmochowski et al., 2012; Cohen and Parra, 2016; Ki et al., 2016). Like other component extraction methods (e.g., PCA, ICA), the CorrCA does this through an eigenvalue decomposition of covariance data, only here, it uses the pooled within-subjects cross covariance

$$R_{w}=\frac{1}{N}\,\sum_{k=1}^{N}R_{k\,k},$$

and between-subjects cross covariance

$$R_{b}=\frac{1}{N\,\left(N-1\right)}\,\sum_{k=1}^{N}\sum_{l=1,l\neq k}^{N}R_{k\,l}$$

where

$$R_{k\,l}=\sum_{t}\left(x_{k}\left(t\right)-{\bar{x}}_{k}\right)(x_{l}\left(t\right)-{\bar{x}}_{l}^{T}$$

to calculate the cross-covariance across all electrodes x and time *t* between participant *k* and *l*. Therefore, eigenvectors w*_*i*_* of the cross-covariance matrix R*_*w*_*^–1^R*_*b*_*, with the largest eigenvalues λ*_*i*_* computed as (R*_*w*_*^–1^R*_*b*_*)w*_*i*_* = λ*_*i*_*w*_*i*_* are the components that maximize Pearson’s rho between subjects (Dmochowski et al., 2012; Cohen and Parra, 2016; Ki et al., 2016). The CorrCA produces *N-1* components that are rank-ordered by the magnitude of their correlation across subjects, where *N* is the number of input sources (electrodes). The spatial weights of the top-ranked group-level component can then be back-projected onto the EEG data from individual subjects—effectively creating a spatial filter of the data—to generate a component time course for each participant. We will then correlate the individual component time courses across the group and compute the average correlation coefficient on a per-subject basis to compute individual inter-subject correlations which reflects the similarity of each participant’s neural activity relative to the group (Cohen and Parra, 2016; Ki et al., 2016; Iotzov et al., 2017).

The reliability of the CorrCA component and the statistical significance of the inter-subject correlations can be established using a leave-one-out variant of the CorrCA and permutation statistics. Specifically, the CorrCA is iteratively calculated on all possible *N-1* subsets of the group. This produces unique components and time courses for each subset which can be used to calculate the average inter-subject correlations for each participant *across* subsets. Statistical significance of the per-subject means inter-subject correlations can then be determined by comparing their magnitude to the top 5% (*p* < 0.05, FDR corrected) of a null distribution of phase-shifted correlation coefficients generated using a 1000 iteration resampling procedure (Theiler et al., 1992). This analysis technique will be applied to the EEG data from individual patients to compare their neural activity during the intact and scrambled versions of *Taken*.

### Neurocognitive and Functional Outcomes

We will prospectively track neurocognitive outcomes up to 12 months post-injury, using the web-based CBS platform (Cambridge Brain Sciences, 2020) (see Figure 3). This will enable patients to complete the tests from any location (e.g., ward, rehabilitation facility, home) without the need to attend clinic, thereby overcoming current limitations of standard cognitive batteries and enabling inclusion of previously inaccessible ICU survivors.

**FIGURE 3 F3:**
[figure not shown]
Schematic timeline of CBS testing and results per trial. Once patients recover consciousness, are delirium free and able to carry out the CBS web-based battery, testing will take place on a daily basis until hospital discharge. After hospital discharge and until 3 months following Trial 1 of CBS testing, testing will take place on a weekly basis. After the first 3 months of testing, CBS tests will then be taken on a monthly basis, up to 12 months following injury. Displayed is a single CBS trial for an ICU patient with a primary brain injury who has recovered consciousness. This patient’s test-specific (lower left) and domain-specific (lower right) results are plotted in relation to normative data for the patient’s age and sex.

Once patients are recruited in the ICU and have recovered consciousness, they will be screened daily for delirium using the Intensive Care Delirium Screening Checklist (ICDSC) (Bergeron et al., 2001). If they score negative, they will be asked to provide written informed consent to continue participation in the study, or to withdraw. If they choose to continue participating in the study, they will be asked to complete an abridged version of the CBS battery on a laptop or tablet (as soon as able). This battery of six tests will take up to 20 min to complete. The tests include: Odd One Out, Rotations, Paired Associates, Grammatical Reasoning, Monkey Ladder, and Digit Span (see Wild et al., 2018). These tasks are designed to assess verbal and deductive reasoning, episodic memory, visuospatial working memory, and short-term memory (see Table 1). CBS testing will be repeated every day during the acute phase (ICU, ward), or as often as possible given the constraints of ICU and ward care. Following hospital discharge, patients will receive a URL link via email to complete the same test series online on a weekly basis for up to three months following their first CBS trial. After this period, patients will be asked to complete neurocognitive tests every month for up to 12 months post-injury.

**TABLE 1 T1:** Tests comprising the abridged version of the Cambridge Brain Sciences battery used in this study.

Name	Descriptions
Odd one out	Based on a sub-set of problems from the Cattell Culture Fair Intelligence Test (Cattell, 1949). Nine groups of colored shapes are displayed in a grid. The features define each group (color, shape, # of items) are related to each other according to a set of rules. Participants must deduce the rules that relate these features and select the group whose contents do not correspond to those rules. They have 90 s to solve as many problems as possible, and the puzzles get progressively more difficult. A correct response increases the final score by one point, whereas an incorrect response decreases the score by one point.
Rotations	Task that measures the ability to spatially manipulate objects in mind (Silverman et al., 2000). On each trial, two groups of colored squares (each with N squares) are displayed beside each other. One of the groups is rotated by a multiple of 90 degrees. The groups are either identical (when un-rotated) or differ by the position of just one item, and participants must indicate if the groups match. They have 90 s to complete as many trials as possible. A correct response increases the final score by N, and the subsequent trial has groups of N+1 squares. If the response is incorrect, the total score decreases by N, and next trial has groups of N-1 squares.
Paired associates	Based on a test commonly used to assess memory impairments in aging clinical populations (Gould et al., 2005). Sets of boxes are displayed at random locations on grid. The boxes open one after another to reveal an icon, after which they close. The icons are then displayed sequentially in the center of the screen, and the participant must select box that contained that icon. If the participant remembers all the icon-location pairs correctly, then the next trial will have one more box. If an error is made the next trial has one less box. The test ends after three errors. The participant’s score is the maximum number of pairs successfully remembered.
Grammatical reasoning	Based on Alan Baddeley’s 3-min grammatical reasoning test (Baddeley, 1968). On each trial, a written statement regarding two shapes is displayed on the screen, and the participant must indicate whether it correctly describes the shapes pictured below. The participant has 90 s to complete as many trials as possible. A correct response increases the total score by one point, and an incorrect response decrease the score by one point.
Monkey ladder	Based on a task from the non-human primate literature (Inoue and Matsuzawa, 2007). Numbered boxes are displayed (at the same time) at random locations within a grid. After a variable interval (number of squares * 900 ms), the numbers disappear leaving only the boxes. Participants must click the boxes in ascending numerical sequence. Difficulty is varied dynamically like in Spatial Span. The test finishes after three errors, and the resulting score is the length of the longest sequence successfully remembered.
Digit span	Based on the verbal working memory component of the WAIS-R intelligence test (Weschler, 1981). A sequence of digits is displayed, one at a time, in green in the center of the screen. Participants must then repeat the sequence of digits by selecting them on the on-screen keyboard. Difficulty is dynamically varied like previous tests, and the test ends after three mistakes. The resulting score is the length of the longest digit sequence successfully remembered.

Functional outcomes will also be assessed through brief phone interviews at 3 months post-recovery of consciousness (i.e., start of CBS testing), and at 6 and 12 months post-injury. The scales used for this assessment will be the Disability Rating Scale and Glasgow Outcome Scale-Extended (Rappaport et al., 1982; Wilson et al., 1998). Pre-injury occupation will be compared to occupation 6 and 12 months post-injury, to assess functional recovery compared to pre-injury status.

### Association Between Demographic/Clinical Characteristics and Patients’ EEG Features and Outcomes

In order to investigate the effect of clinical and demographic characteristics on EEG reconfiguration during interruption of sedation and on cognitive recovery trajectories, linear regression will be performed separately for each of these variables, with models constructed as follows: the variables sex (male/female), bilingualism (monolingual/multilingual), presence of pre-morbid neurocognitive or psychiatric disorder (presence/absence), presence of visual fixation at 24 h post-injury (yes/no), presence of delirium (yes/no), and presence of elevated intracranial pressure (yes/no) will be used as binary regressors. The variables age (mean-centered across entire sample), education, ethnicity, injury type, GCS at admission, severity illness score, Marshall and Rotterdam scores, duration of elevated intracranial pressure, delirium duration post-traumatic amnesia duration, ICU stay duration, and hospital stay duration will be treated as categorical, with n-1 regressors. All statistical tests will be corrected for multiple comparisons using a False Discovery Rate across scores, and separately for each effect. We include measures of standardized and unstandardized effect sizes, confidence intervals, and Bayes factors.

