#### Participants

Two hundred (*n* = 200) brain-injured patients in a pharmacologically-induced coma will be recruited from three ICUs in Montreal, QC, Canada (the Montreal General Hospital, the Montreal Neurological Hospital, the Royal Victoria Hospital) and two ICUs in London, ON, Canada (University Hospital and Victoria Hospital). Sample size was determined based on feasibility (i.e., number of patients in this condition per ICU on a yearly basis, estimated patient survival rates) and the fragile medical state of our study population. Considering that several patients may not survive their injury and/or may withdraw from the study prior to the 12-month follow-up, we aim to have 200 patients initially included in order to have 100 patients complete the entire study (up to 12 months post-injury).

Patients will be included if they have suffered a brain injury (e.g., traumatic brain injury, anoxic brain injury, stroke, subarachnoid hemorrhage); are continuously sedated; are between 24 h and 7 days post-injury; are aged between 18 and 70 years of age; and have a planned interruption of sedation for clinical assessment. Patients will be excluded if: they are not native English or French speakers; they are deemed medically unsuitable by the attending physician; there are barriers to appropriate application of the high-density EEG net (e.g., scalp infections, burns); they have a history of pre-existing dementia or mild cognitive impairment; they show presence of *status epilepticus*; they are on contact precautions (e.g., methicillin-resistant *Staphylococcus aureus*, COVID-19), which require an extraordinary disinfection protocol for testing equipment.

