As this is a prognostic study on acute ICU patients, we expect that a large proportion of our patients will not survive. However, this study will monitor all patient outcomes, including death. Indeed, we expect our EEG features to be associated to all patient outcomes, from death to full cognitive recovery. We also expect to have some patients with promising EEG findings for whom there will be a decision for withdrawal of life sustaining therapies based on patient values. Based on a recent meta-analysis, average mortality rates for severe traumatic brain injury was 39% while unfavorable outcome was 60% (Rosenfeld et al., 2012). Thus we anticipate approximately 50% of our initial sample (*n* = 100) will be able to complete neurocognitive testing. In itself, this is a larger sample size than most studies that prospectively assess ICU patient populations.

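### Age, ordered scores and durations are listed as categorical with n-1 dummies: this contradicts the mean-centring of age, discards order, and costs power according to the number of levels

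*Protocol article*

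**What the plan says.** The Protocol article, section Association Between Demographic/Clinical Characteristics and Patients' EEG Features and Outcomes, plans linear regressions with two kinds of response: EEG reconfiguration during interruption of sedation, and cognitive recovery trajectories. On structure it says "linear regression will be performed separately for each of these variables".

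Six yes/no characteristics enter as binary regressors. A second list opens with "The variables age (mean-centered across entire sample), education, ethnicity, injury type, GCS at admission, severity illness score, Marshall and Rotterdam scores". It continues with the durations of elevated intracranial pressure, delirium and post-traumatic amnesia, and closes with "ICU stay duration, and hospital stay duration will be treated as categorical, with n-1 regressors". No levels, bands or cut-points are given.

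On numbers, the Participants section says "we aim to have 200 patients initially included in order to have 100 patients complete the entire study" and gives the basis as "Sample size was determined based on feasibility". Eligible patients "are aged between 18 and 70 years of age". No power, effect size or FDR level is stated for these regressions.

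**The concern.** There are three problems.

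- **Age is given two incompatible codings.** Centring on the sample mean shifts the zero of a numeric regressor. A set of category indicators has no mean to subtract. An analyst cannot carry out both instructions.
- **Ordered quantities are coded as if unordered.** GCS, the severity score, the CT scores and lengths of stay have a direction. Dummy coding ignores it, spreads one trend over many coefficients, and tests them jointly at a cost in power that grows with the number of levels.
- **Some regressors come after one of the responses.** ICU stay, hospital stay, amnesia duration and later delirium are completed after an EEG taken between 24 h and 7 days. They cannot explain EEG reconfiguration, although the text speaks of an effect on it. Stay is also cut short by death, which the article expects to be common.

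Under Anticipated Results, the article expects to identify characteristics that mediate or moderate recovery. With this coding, moderate trends could be missed and read as absence of association.

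**Working it through.** **The plan's own figure.** Under Anticipated Results: "Thus we anticipate approximately 50% of our initial sample" will complete neurocognitive testing. 200 × 0.50 = 100, which reproduces. I therefore use n=100 for cognitive responses and n=200 for EEG responses, which are recorded at enrolment.

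**Number of dummies (levels minus one).**
- Age: 18 to 70 gives 53 whole years, so at most 52 dummies. If ages are uniform (assumed), the expected number of distinct ages is 53 × (1 − (52/53)^n): 45.1 at n=100 and 51.8 at n=200, so about 44 and 51 dummies.
- Durations in whole days, unbinned: assuming a lognormal spread with median 10 to 30 days, about 29 to 57 dummies at n=100 and 36 to 81 at n=200.
- Scores, with ranges assumed because the article gives none: Marshall and Rotterdam 6 levels each, so 5 dummies; GCS 13 levels, so 12 dummies; severity score up to about 24 dummies.

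**Power of the overall F-test.** Assumed: true linear correlation r = 0.30 and alpha = 0.05 before FDR. The noncentrality is λ = n·r²/(1 − r²), with df1 = k and df2 = n − k − 1.
- n=100: λ = 100 × 0.09/0.91 = 9.89
- n=200: λ = 200 × 0.09/0.91 = 19.78

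| Coding | k | n=100 | n=200 |
|---|---|---|---|
| One linear term | 1 | 88% | 99% |
| 6-level score | 5 | 64% | 94% |
| 13-level score | 12 | 44% | 84% |
| Longer score or coarse days | 24 | 29% | 67% |
| Many distinct values | 44 | 17% | 48% |
| Whole-year age at n=200 | 51 | – | 43% |

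**Sensitivity to effect size.** If the effect is instead set so that one linear term has 80% power (R² = 0.074 at n=100, 0.038 at n=200), the power left is:
- k=5: 54% and 55%
- k=12: 36% and 38%
- k=24: 23% and 26%
- k=52: 12% and 16%

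A simulation with whole-year ages and nearly the same effects gives 80% falling to 15% at n=100, and 79% to 16% at n=200. With a strong effect (R² = 0.15), power falls from 99% to 32% at n=100, but only from 100% to 77% at n=200.

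**Timing.** The EEG is taken between 24 h and 7 days after injury or ICU admission. Under Neurocognitive and Functional Outcomes, daily delirium screening starts once consciousness is recovered. Total ICU and hospital stay are known only at discharge or death. For EEG reconfiguration as the response, these variables lie downstream. For cognitive trajectories they do not raise the same difficulty.

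**The case against.** The article is condensed, and a fuller document may define bands. With a few bands per duration the loss is modest, and the text does not exclude this. That stands: the large losses are conditional on unbinned coding. It does not rescue the sentence, because a coding rule is stated, it is incompatible with centring age, and bands would still discard order.

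The mean-centring suggests that age was meant to be continuous and simply sits in the wrong list. That is the more natural reading, and on it age loses no power. What remains for age is a contradiction to correct, so the age-based power figures should not be the headline.

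A reader might infer that every listed variable spends dozens of degrees of freedom and loses most of its power. That does not hold for the short scores: with r = 0.30, 5 dummies keep 64% at n=100 and 94% at n=200, and 12 dummies keep 84% at n=200.

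A reader might also infer that the regressors would outnumber the patients so that the model could not be fitted. That would need all characteristics in one model. The text says "linear regression will be performed separately for each of these variables", most naturally one model per characteristic, so the degrees of freedom are not added up.

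Finally, the section heading speaks of association, which softens the timing point. Stay and amnesia duration are reasonable regressors for cognitive trajectories. The objection to them is confined to the EEG response.

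**Conclusion.** The point holds in a limited form. The sentence contradicts itself on age and assigns ordered scores and durations to dummy coding, without stating levels. The cost runs from moderate to severe with the number of levels: at n=100, from 88% down to 64% for a 6-level score, 44% for a 13-level score, and 29% to 17% for 24 to 44 dummies; at n=200, from 99% down to 94%, 84%, and 67% to 48%.

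These figures assume r = 0.30, alpha 0.05 before FDR, a truly linear relation, and the score ranges and unbinned values described above. The article gives no effect size or score ranges.

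It should be fixed, but it does not threaten the main analysis. It would be wrong to read these regressions as the study's second aim: the aims in the Introduction concern EEG markers that capture reorganization and predict recovery, and the classification analysis serves those. The regressions are supporting association analyses, and no power is claimed for them.

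**What to change.** Rewrite the paragraph on regressors:

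- Enter age as one continuous term, centred on the sample mean.
- Enter durations as continuous terms, transformed if skewed.
- Enter GCS, severity, Marshall and Rotterdam scores as linear or ordinal terms.
- Keep n-1 dummies for ethnicity, injury type and, if recorded in bands, education.
- If any duration is to be banded, state the cut-points in advance.
- Where EEG reconfiguration is the response, leave out ICU stay, hospital stay, amnesia duration and delirium arising after the recording, or report them only as associations. They may stay in the cognitive-trajectory models.
- State whether there is one model per characteristic or one per response.

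The cost is one reworded paragraph and no new data. The small downside is that a linear or smooth form is assumed; a transformation or smooth term can be specified where that is doubtful.

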### Anticipated Results

Our general hypothesis is that the brain’s ability for adaptive network reconfiguration upon interruption of continuous sedation will be associated to the eventual recovery of consciousness and to more favorable cognitive and functional outcomes. We expect that patients who recover consciousness and demonstrate the strongest cognitive recovery will have brain network and connectivity markers that re-appear during the brief interruption of continuous sedation. More specifically, we expect the re-appearance of feedback-dominant connectivity between the frontal and parietal regions and the presence of posterior alpha network hubs to be strongly associated to patient prognosis (i.e., recovery of consciousness and cognitive functions) (Figure 4).

